**Table 5 Tab5:** **Number and type of serious adverse events**

Type of SAE* -% n/N	Ceftriaxone + standard care (n = …)	Standard care (n = …)	***P***
- Death			
- Life-threatening event			
- New hospitalization			
- Prolongation of existing hospitalization			
- Persistence of significant disability or incapacity			
Total number of SAE’s			

*SAE, serious adverse event.

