**Results:**

The primary outcome is the score on the modified Rankin Scale (mRS), assessed by ordinal logistic regression analysis according to a proportional odds model. Secondary analysis of the primary outcome is the score on the mRS dichotomized as a favorable outcome (mRS 0 to 2) versus unfavorable outcome (mRS 3 to 6). Secondary outcome measures are death rate at discharge and 3 months, infection rate during hospital admission, length of hospital admission, volume of post-stroke care, use of antibiotics during hospital stay, quality-adjusted life years and costs. Complications of treatment, serious adverse events (SAEs) and suspected unexpected serious adverse reactions (SUSARs) are reported as safety outcomes.

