### Assessment of safety outcomes

Safety outcomes are complications of treatment, SAEs and SUSARs. All SAEs and SUSARs during the hospital stay are recorded in case record forms by the treating physician and reported to the trial office. SAEs and SUSARs occurring after discharge are recorded during the follow-up interview at 3 months. The physician records treatment complications in the CRF (diarrhea caused by *C. difficile*, allergic reaction that caused cessation of ceftriaxone, infection with ceftriaxone resistant microorganism, phlebitis at place of IV-catheter, elevation of liver enzymes, oliguria or elevation of serum creatinine).

Cause of death will be reviewed by two independent observers. They will use information from the hospital discharge letter or the medical correspondence received by the general practitioner in case the patient died after discharge. Discrepancies will be reviewed in a consensus meeting in the presence of a third investigator. Outcome parameters were derived from three recent cardiovascular trials and were modified for expected outcomes in our study
[14–16]. A distinction will be made among a cardiovascular cause (brain infarction, brain hemorrhage, myocardial- or pulmonary embolism. or another cardiovascular cause), an infection (pneumonia, sepsis or another infection), death by any type of malignancy, death by any other cause (for example, traffic accident), withdrawal of treatment due to a poor prognosis or unknown cause of death.

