### Safety outcomes

Complications of treatment, SAE’s and SUSAR’s per patient will be tabulated according to treatment group, and analyzed using the chi-squared test (Table 
5 and table 
6).

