**Table 6 Tab6:** **Complications of treatment**

Adverse reaction - % n/N	Ceftriaxone + standard care (n = …)	Standard care (n = …)	***P***
- Diarrhea caused by *C. difficile*			
- Allergic reaction that caused cessation of ceftriaxone			
- Infection with ceftriaxone-resistant microorganism			
- Phlebitis at place of IV-catheter			
- Elevation of liver enzymes			
- Oliguria or elevation of serum creatinine			

Total number of adverse reactions - number %.

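### Table 5 breaks serious adverse events down only by seriousness criterion and total, so a serious harm outside Table 6's six complications and not reported as a SUSAR can be diluted or offset

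*SAP article*

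**What the plan says.** All references are to the SAP article.

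- **Table 5** is titled "Number and type of serious adverse events". Its rows are death, life-threatening event, new hospitalization, prolongation of hospitalization, and "Persistence of significant disability or incapacity". A last row gives the total number of SAEs. The heading asks for a percentage with n/N, and there is a P column.
- **Safety outcomes** states that complications, SAEs and SUSARs "per patient will be tabulated according to treatment group, and analyzed using the chi-squared test".
- **Table 6** lists six complications by arm with P values, among them "Infection with ceftriaxone-resistant microorganism".
- **Assessment of safety outcomes** gives the source of that list: "The physician records treatment complications in the CRF". It also says: "Cause of death will be reviewed by two independent observers". Categories of death are defined, but no table or comparison by arm is assigned to them.
- **Abstract, Results** shows the overlap with efficacy: "Secondary outcome measures are death rate at discharge and 3 months, infection rate during hospital admission, length of hospital admission". The section on death rate adds that in-hospital deaths are notified as SAEs.

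Neither Table 5 nor Table 6 has a SUSAR row. The article states no expected SAE rate.

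**The concern.** A seriousness criterion says why an event had to be reported, not what happened. From Table 5 alone a reader could not tell a serious drug reaction from a recurrent stroke if both prolonged the admission. The title promises types, and the rows do not give them.

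In this trial that has two consequences. A modest drug-related excess is diluted in a row that also counts background events. And since the hypothesis is that ceftriaxone improves outcome by preventing infection, a fall in background events could offset the excess in the same row. At stake is the safety conclusion, not the primary efficacy result: the table could show no difference in SAEs while one specific serious harm differed between the arms.

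A smaller point concerns the unit of analysis. The text and the column heading point to patients, while the label of the last row points to events. With a P column beside it, the unit to be tested is not fixed.

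**Working it through.** **The plan's own figure.** The SAE comparison has no stated rate, power or detectable difference, so there is nothing to reproduce. The 2,550 patients belong to the primary analysis and serve here only to set the scale.

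**Where a serious event would appear**

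| Kind of event | Place in the plan |
|---|---|
| One of the six complications | Own row in Table 6, with P |
| SUSAR | Promised in the text; no row in Table 5 or 6 |
| Death | Table 5 row and mortality outcome; cause classified but not assigned to a table |
| Any other non-fatal SAE | Seriousness rows and total of Table 5 only |

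The last line is the gap.

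**Inputs for an illustration**

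- n = 2,550 / 2 = 1,275 per arm (total and 1:1 allocation from Summary study protocol). Safety is analysed per protocol, so the real n is somewhat smaller.
- Two-sided level 0.05. The plan states it for the primary analysis; its use here is an assumption.
- Assumed background: 10–40% of patients with any SAE; 0.2–1% with one specific type of event.
- Assumed true excess d = 1 percentage point.

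**Formula.** With p1 and p2 the two proportions and p̄ their mean:

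SE0 = √[2 p̄(1 − p̄)/n], SE1 = √[(p1(1 − p1) + p2(1 − p2))/n], power = Φ((d − 1.96 SE0)/SE1).

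- Own row, 0.2% vs 1.2%: SE0 = 0.00330, SE1 = 0.00330; (0.01 − 0.00647)/0.00330 = 1.07; power 86%.
- Total row, 30% vs 31%: SE0 = 0.01823, SE1 = 0.01823; (0.01 − 0.03574)/0.01823 = −1.41; power 8%.

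| Row | Background vs with 1-point excess | Power |
|---|---|---|
| Own event type | 0.2% vs 1.2% | 86% |
| Own event type | 0.5% vs 1.5% | 72% |
| Own event type | 1% vs 2% | 55% |
| Any SAE | 10% vs 11% | 13% |
| Any SAE | 20% vs 21% | 9% |
| Any SAE | 30% vs 31% | 8% |
| Any SAE | 40% vs 41% | 7% |

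The difference detectable with 80% power is 0.9 to 1.5 points in a specific row (background 0.2% to 1%) and 3.6 to 5.5 points in the total (background 10% to 40%).

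**Offsetting.** If 1 point of other SAEs is prevented, the net difference in the total is 1 − 1 = 0, and the test rejects only at its 5% level.

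**Multiplicity.** Take eight event types as an example. Eight independent tests at 0.05 give 1 − 0.95^8 = 34% chance of at least one false signal. At 0.05/8 the own-row power falls from 86% to 62% (0.2% vs 1.2%) and from 72% to 42% (0.5% vs 1.5%). The gain shrinks but remains.

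**The case against.** The strongest reply is that safety does not rest on Table 5. Table 6 compares *C. difficile* diarrhea, allergic reaction causing cessation, resistant infection, phlebitis, liver enzymes and renal abnormality by arm. A suspected and unexpected serious reaction is by definition a SUSAR, and the text promises to tabulate and test these. Deaths get a two-observer review of cause. This stands. A reader might infer that any real drug-related excess is hidden; the article does not support that. The gap is limited to serious events outside the six items and not reported as SUSARs.

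Three other tempting readings also go too far:

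- *That stroke outcomes dominate the rows.* No SAE rates are given, so the article shows only that the rows can mix such events with drug harm.
- *That several rows restate efficacy outcomes.* Only death is shown to be both an outcome and an SAE. A reported prolongation is not length of stay in days, and a reported disability event is not the blinded mRS interview.
- *That event counts will be tested as if independent.* The text and the heading say otherwise. What stands is an ambiguous row label.

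The objection is also right that the power contrast flatters event-type rows by placing the whole excess in one rare row without correction. And a line for SAEs excluding trial outcomes would need attribution of events recorded by physicians who know the allocation, which could add bias.

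It might finally be said that a table shell in a condensed article does not rule out further listings. True, but the article prints this table, labels its rows as types and assigns it a test.

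**Conclusion.** The concern holds in this limited form. Followed as printed, Table 5 cannot separate a specific serious non-fatal harm from other events that meet the same criterion. Such a harm, if outside Table 6 and not a SUSAR, can be diluted or offset. Under the assumed rates, a 1-point excess that would be seen with roughly 55–86% power in its own row is seen with about 7–13% power in the total. The direction is the same across the whole assumed range; the exact figures depend on background rates that the article does not give, on one event type carrying the whole excess, and on no multiplicity correction. The unit of the total row needs to be fixed, and the promised SUSAR comparison has no place in the printed tables. The primary analysis and the sample size are unaffected. This is an inexpensive improvement to safety reporting, not evidence that a harm exists or would go wholly unreported.

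**What to change.** Before the code is broken:

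1. Add rows to Table 5 for patients with at least one SAE, by clinical event type and arm. Classify the events blind to allocation, from a category list fixed in advance, and count each patient once per row.
2. Present these rows descriptively, with differences and 95% confidence intervals rather than a test for each.
3. Make the tested total the number of patients with any SAE, and list the total number of events without a P value.
4. Add the SUSAR row that the Safety outcomes section promises.
5. Show the cause-of-death categories from Assessment of safety outcomes by arm.
6. Keep the seriousness-criterion rows as a supplement.

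Do not add a line for SAEs excluding trial outcomes unless objective, blinded rules define which events are removed.

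The cost is a little coding of reports that already go to the trial office, and a longer table. The downside is that more rows raise the chance of a false signal if each is tested, hence the descriptive presentation.

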**Table 6 Tab6:** **Complications of treatment**

Adverse reaction - % n/N	Ceftriaxone + standard care (n = …)	Standard care (n = …)	***P***
- Diarrhea caused by *C. difficile*			
- Allergic reaction that caused cessation of ceftriaxone			
- Infection with ceftriaxone-resistant microorganism			
- Phlebitis at place of IV-catheter			
- Elevation of liver enzymes			
- Oliguria or elevation of serum creatinine			

Total number of adverse reactions - number %.

### Subgroup analysis of primary and secondary outcomes

We will perform the following sub-group analyses for the primary outcome: stroke type (infarction or hemorrhage), stroke severity (NIHSS 1 to 9 or NIHSS 10 to 30), time between stroke symptoms and start of the antibiotic treatment (0 to 12 h versus 12 to 24 h) and age. For the subgroup analysis of primary analysis of primary outcome, the single OR from the proportional odds model will be calculated for each subgroup separately. For the subgroup analysis of secondary analysis of primary outcome, we will tabulate the results and analyze them using the chi-squared test and presented as OR and 95% CI ((Table 
7: subgroup analysis of primary outcome). In addition to these predefined subgroup analyses, we will perform a larger set of exploratory additional analyses. For secondary outcomes, we will perform all the previous mentioned subgroup analyses (stroke type, severity, time to treatment, and age). In addition we will perform analysis on presence of a swallowing disorder, respiratory tract infections, and a urinary catheter.

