### Summary study protocol

PASS is a multicenter prospective, randomized, phase III, open-label, blinded end-point superiority trial (PROBE) of standard care with preventive ceftriaxone treatment compared to standard care without preventive ceftriaxone. Adult patients with stroke (both ischemic and hemorrhagic), a score ≥1 on the National Institutes of Health Stroke Scale (NIHSS) and stroke onset within 24 hours were included
[8]. Patients were excluded in case of infection at admission, use of antibiotics within 24 hours before admission, previous hypersensitivity or anaphylaxis to cephalosporins or penicillin, subarachnoid hemorrhage, pregnancy or when death seemed imminent. Patients were randomly assigned to either ceftriaxone at a dose of 2 g, given every 24 h intravenously for 4 days, in addition to stroke-unit care, or standard stroke-unit care without preventive antibiotic therapy. Randomization was performed through ALEA (online software for randomized trials;
https://nl.tenalea.net/amc/ALEA/Login.aspx) and is based on a uniform distribution; weight of the arms is equal (1:1). Randomization is stratified according to study center (academic hospital, large non-academic hospital, or small non-academic hospital) and stroke severity (score on NIHSS 1 to 9 or >9) and performed by using random blocks with a maximum block size of 6; blocks of 2, 4 and 6 are made per stratum combination

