### Protocol deviations in eligibility, consent procedure, treatment

When a patient was randomized but did not adhere to inclusion or exclusion criteria, this was considered a protocol deviation regarding eligibility. Patients with protocol deviations in eligibility were included in the ITT analysis, but excluded from PP analysis.In each center, the local investigator obtained written informed consent from the patient or representative according to the PASS study protocol. Patients who withdrew consent directly after randomization were excluded from further analysis. The flow of patients is displayed in the CONSORT flowchart (Figure 
1).

Treatment allocation was regarded as carried out according to the study protocol when a patient randomized for ceftriaxone in addition to standard care received ceftriaxone 2 gram each 24 hours for 4 days. Patients were also considered as treated PP when treatment was terminated within 4 days due to discharge, death, a palliative care policy, an allergic reaction without anaphylaxis or a previous allergic reaction in medical history (see inclusion and exclusion criteria and protocol deviation in eligibility), other side effects of treatment, or when treatment with ceftriaxone was changed into treatment with another antibiotic because of an infection because these situations and what to do were all defined and described in the initial protocol
[6]. In patients allocated to standard care, treatment was carried out according to the study protocol when patients did not receive preventive antibiotic therapy.

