**Table 7 Tab7:** **Subgroup analysis of primary outcome**

	Ceftriaxone + standard care (n = …)	Standard care (n = …)	***P***	OR 95% CI
Favorable outcome (mRS* 0 to 2) - % n/N				
- Ischemic stroke				
- Hemorrhagic stroke				
- Transient ischemic attack (TIA)				
- Other				
Favorable outcome (mRS 0 to 2) - % n/N				
- NIHSS** 1 to 9				
- NIHSS 10 to 30				
Favorable outcome (mRS 0 to 2) - % n/N				
- time to treatment 0 to 6 h				
- time to treatment 6 to 12 h				
- time to treatment 12 to 24 h				

*mRS, denotes modified Rankin Scale.

**NIHSS denotes National Institutes of Health Stroke Scale.

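### The time-to-treatment subgroup is defined by an event that standard-care patients do not have, so its odds ratio cannot be formed as written; separately, the text and Table 7 give different time bands.

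*SAP article*

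**What the plan says.** The section on subgroup analysis of primary and secondary outcomes lists four predefined subgroup variables. One is "time between stroke symptoms and start of the antibiotic treatment (0 to 12 h versus 12 to 24 h". For the ordinal analysis, "the single OR from the proportional odds model will be calculated for each subgroup separately". For the dichotomized outcome, the plan is a chi-squared test and an odds ratio with its 95% confidence interval in each subgroup. The same section carries time to treatment over to the secondary outcomes.

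Table 7 is the shell for the dichotomized version. It has a ceftriaxone column, a standard-care column, a P value and an odds ratio. Its time rows are "time to treatment 0 to 6 h", "time to treatment 6 to 12 h" and "time to treatment 12 to 24 h".

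The Summary study protocol describes the control arm as "standard stroke-unit care without preventive antibiotic therapy". The section on protocol deviations adds: "In patients allocated to standard care, treatment was carried out according to the study protocol when patients did not receive preventive antibiotic therapy".

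The section defining the analysis populations keeps patients who crossed over immediately, and so did not get their allocated treatment, in the intention-to-treat population.

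**The concern.** A subgroup odds ratio compares the two randomized arms within a class, so every patient in both arms must be classifiable, preferably by something fixed before treatment. Start of preventive antibiotics occurs after randomization and, by design, in one arm only. The standard-care cells in the time rows of Table 7 have no defined content. An analyst who has to fill them must invent a rule, and some rules would break the randomized comparison within each class.

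A second, independent problem is that the text and Table 7 divide time differently. The split to be reported is therefore not fixed in advance and could be chosen after the results are seen.

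**Working it through.** The SAP states no figure for this subgroup, so there is none to reproduce. The check is a comparison of sections, followed by an illustration.

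**1. Who has a value for the subgroup variable?**

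- Standard care, managed as allocated: no preventive antibiotic, hence no start time. With 1:1 allocation of 2,550 patients this is about 2,550 / 2 = 1,275 patients.
- Ceftriaxone, crossed over immediately: kept in the intention-to-treat population, no start time. The number is not given.
- Ceftriaxone, treated: start time exists.

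As written, no control managed to plan can be placed in any band, so no within-band odds ratio has a comparator. This follows from the definition alone, whichever bands are used.

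**2. What if the arms are put on different clocks?**

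The SAP does not propose this; it is one way an analyst might fill the gap. Controls are classed by onset to randomization, and ceftriaxone patients by onset to first dose. Assumptions: onset-to-randomization is uniform over 0 to 24 h, and there is a fixed delay of d hours from randomization to first dose.

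Ceftriaxone patients who cross the 12 h cut-point are those randomized between 12 − d and 12 h. As a share of all ceftriaxone patients this is d/24. As a share of those randomized within 12 h it is d/12.

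| d | Share of all ceftriaxone patients (d/24) | Share of the 0 to 12 h class (d/12) | Controls moved |
|---|---|---|---|
| 1 h | 4% | 8% | 0 |
| 2 h | 8% | 17% | 0 |
| 4 h | 17% | 33% | 0 |

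To see what this does to an odds ratio, assume further that there is no treatment effect, that the favorable-outcome rate averages 60%, and that it falls linearly by b over 24 h. For d = 4 h and b = 20 points, the rate at time t is 0.70 − 0.20 × t/24:

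- Early band. Controls span 0 to 12 h (mean 6 h): 0.650. Ceftriaxone patients were randomized at 0 to 8 h (mean 4 h): 0.667. Odds ratio = (0.667/0.333) / (0.650/0.350) = 1.08.
- Late band. Controls span 12 to 24 h (mean 18 h): 0.550. Ceftriaxone patients were randomized at 8 to 20 h (mean 14 h): 0.583. Odds ratio = (0.583/0.417) / (0.550/0.450) = 1.15 (1.145 before rounding).

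Over d = 1 to 4 h and b = 0 to 20 points, the null odds ratio lies between 1.00 and 1.08 (early) and between 1.00 and 1.15 (late). With no gradient it stays at 1.00. These odds ratios are for the dichotomized outcome. With both arms classed by onset to randomization, the null value is 1.00 in every band.

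**3. Bands in the text and in Table 7**

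| Place | Bands |
|---|---|
| Text of the subgroup section | 0 to 12 h; 12 to 24 h |
| Table 7 | 0 to 6 h; 6 to 12 h; 12 to 24 h |

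The bands are nested: the first two rows of the table make up the first band of the text, and the last band is the same. Adjacent bands share a limit (12 h in both places, and 6 h in the table), so a patient exactly at the limit belongs to two. Nothing says which split is prespecified.

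**The case against.** The strongest counter-argument is about reach. This is one of four predefined subgroup variables. The primary proportional-odds analysis by intention to treat and the overall analyses of secondary outcomes do not use it. The mixed-clock bias depends on a rule that the SAP does not state and on an assumed time distribution, delay and outcome gradient; it is modest in the range shown and absent without a gradient. All of this stands, and it limits the weight of the point.

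It can also be said that an article condenses a fuller protocol, which may give controls a reference time. That is possible. However, the article does not leave the variable open: it fixes it as the start of antibiotics and refers to no rule for the other arm.

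Some stronger readings are tempting but unsupported:

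- A reader might infer that the differing bands cause the missing comparator. They do not. Because they are nested, the freedom they leave is one extra split of the early band.
- A reader might take the 17% for a 2 h delay as a share of all ceftriaxone patients. It is a share of the 0 to 12 h class; the share of all is 8%.
- A reader might conclude that some patients were dosed after 24 h and so fall in no band. The 24 h limit is stated for inclusion and the SAP gives no limit for the first dose, so this could happen, but the document does not show that it did.
- A reader might add deaths before the first dose to those without a start time. The SAP mentions death only as a reason for ending treatment early.

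**Conclusion.** Wrong as written, and it should be fixed. The time subgroup has no value for standard-care patients managed as allocated (about 1,275 under equal allocation) or for ceftriaxone patients who crossed over at once, so the planned odds ratio cannot be formed. This conclusion needs no numerical assumption. The shares crossing 12 h and the shifted null odds ratios are illustrations that rest entirely on the assumptions stated with them.

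The two-band and three-band versions are a separate contradiction, minor in extent, that leaves the prespecified split undetermined.

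It would go too far to infer that the trial's main result is at risk. The effect is confined to this subgroup analysis and its repetition for the secondary outcomes.

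**What to change.** - Define the subgroup in both arms as time from stroke onset to randomization, which is fixed before treatment and can be defined for every patient.
- Choose one set of bands and use it in the text and in Table 7. Write the limits so that they do not overlap, for example up to and including 12 h versus more than 12 h if two bands are kept.
- State where patients with onset more than 24 h earlier are placed. Table 1 provides a row for this eligibility deviation, and such patients stay in the intention-to-treat population.
- Apply the same definition to the secondary-outcome subgroups.
- Report onset to first dose descriptively, in the ceftriaxone arm only.

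The cost is a few sentences and one table shell, with no new patients or visits. It assumes that times of onset and randomization were recorded; the SAP says that randomization ran through an online system but does not list the stored fields. The change can be made before results are known, because the SAP states that the code stays unbroken until the paper is accepted.

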[9]. The study has a PROBE design, which implies that blinding is lost, but only as to treatment. Patient and physician were aware of treatment allocation; however, the assessors of outcome were not. Data were collected on admission, during hospital stay, and at 3 months by standardized case record forms. The primary outcome is functional outcome at 3 months follow-up, as assessed on the mRS during a structured telephone interview by a trained assessor blinded for treatment allocation. Secondary outcomes are death rate at discharge and at 3 months, infection rate during hospital admission, length of hospital admission, volume of post-stroke care, use of antibiotics during hospital stay, quality adjusted life years (QALYs) and costs. Safety outcomes are complications of treatment, Serious adverse events (SAEs) and suspected unexpected serious adverse reactions (SUSARs). In the initial trial protocol, we presented a binary logistic regression analysis on the dichotomized mRS (0 to 2 versus 3 to 6) as primary outcome, requiring a sample size of 3,200 patients, and a proportional odds model in a secondary analysis of the primary end point
[9]. Blinded for any of the outcomes, we have changed the primary analysis in PASS from a binary logistic to an ordinal logistic regression on the original mRS, enhancing statistical power. The adapted power analysis showed that with identical assumptions on the clinical effect, using a 0.05 two-sided significance level and 80% study power, 2,550 patients were needed
[9]. The analysis of dichotomized mRS data will now be the secondary analysis of the primary end point.

On 23 March 2014, all patients were included and the last follow-up is expected in June 2014. For the complete study protocol and update, we refer to previous publications
[6, 7].

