### Protocol developments

PASS is registered at current controlled trials (
http://www.controlled-trials.com; ISRCTN: 66140176; date of registration: 6 April 2010). The medical-ethical board of the Academic Medical Center, Amsterdam, approved the protocol on 5 May 2010, and 29 Dutch participating centers were added in the course of the study. Due to the change in primary analysis of primary outcome from a binary logistic approach to an ordinal logistic regression analysis and an expected rate of patients lost to follow-up and/or patients with incomplete data of 5%, the total sample size was reduced from 3,200 patients to 2,550 patients in 2014
[7]. Importantly, no changes were made regarding the primary outcome measurement (that is, the assumed size of the effect on the mRS). This update of the protocol was recently published in this journal
[7].

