### Baseline characteristics

Baseline characteristics of all patients will be outlined per treatment allocation in a baseline table describing the following variables: age, sex, medical history (atrial fibrillation/flutter, stroke, hypercholesterolemia, hypertension, myocardial infarction, cardiac valve insufficiency/stenosis/replacement, peripheral vascular disease, obstructive pulmonary disease, and immunocompromised), current smoking, specific medication (anticoagulants, antiplatelet, statin, ACE inhibitor, ß-blocker, and proton pump inhibitor) prior to stroke, disability prior to stroke on mRS, stroke severity on NIHSS, performance of a screening test for swallowing function, dysphagia, acute treatment (IV thrombolysis and anticoagulant antagonist therapy) and diagnosis at discharge (infarct, haemorrhage, TIA, or other). Outline of the table is displayed in the ‘Outline of figures and tables’ section (Table 
3). All variables will be presented categorized by treatment arm. Dichotomous variables will be displayed in percentage with the number of patients divided by the total number of evaluated patients. Continuous variables will be reported as means with standard deviations when normally distributed and in medians with interquartile ranges when they do not meet the criterion of being normally distributed, as assessed by the Kolmogorov-Smirnov test. For continuous variables, the number of patients evaluated will be presented in a footnote of Table 
3.

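### Subgroups are assessed only by separate odds ratios per level, with no test of whether the treatment effect differs, and the subgroup definitions conflict between the text, Table 7 and the randomization strata

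*SAP article*

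**What the plan says.** The section on subgroup analysis names four factors for the primary outcome: stroke type, stroke severity, time to treatment and age. For the ordinal analysis, "the single OR from the proportional odds model will be calculated for each subgroup separately". For the dichotomized mRS, each subgroup is tabulated and analyzed with a chi-squared test, an odds ratio and a 95% CI, with reference to Table 7. That table has a P column and an odds ratio column, and its blocks are headed "Favorable outcome (mRS* 0 to 2) - % n/N". The four factors are then to be repeated for the secondary outcomes.

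The text available names no interaction term, heterogeneity test or multiplicity rule for subgroups. A short piece directly after Table 7 is missing from the copy reviewed, so absence is judged on the rest.

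The subgroup section defines "stroke severity (NIHSS 1 to 9 or NIHSS 10 to 30", whereas randomization was stratified by "stroke severity (score on NIHSS 1 to 9 or >9". Eligibility required an NIHSS of at least 1, and no upper limit is stated.

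**The concern.** A subgroup analysis asks whether the treatment effect differs between levels of a factor. An odds ratio within each level, with or without a P value, does not test that. One level can be significant and another not simply because each holds only part of the trial's information. A table with a P value per row and no interaction P gives the reader nothing else to go on.

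The article's stated reason for publishing is to fix the analyses before any outcome is known. Where text and table define the same subgroup differently, the choice remains open after unblinding. At stake is the reliability of any statement about subgroup differences, not the primary result.

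**Working it through.** **Inputs.** From the Summary study protocol: "using a 0.05 two-sided significance level and 80% study power, 2,550 patients were needed", with equal allocation. The article leaves the event rates, common odds ratio and mRS distribution to its earlier publications, so 2,550 cannot be reproduced here. That is not a fault, and the check needs only alpha and power. Subgroup shares are not given; I assume a range.

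**Overall effect in standard-error units.** 1.960 + 0.842 = 2.802. Check: Φ(2.802 − 1.960) = 0.80.

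**Uniform effect, ordinal analysis.** A subgroup with share f of the information has power Φ(2.802·√f − 1.960); the opposite tail is negligible. With powers p1 and p2, the chance that exactly one is significant is p1(1 − p2) + p2(1 − p1).

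| Split | Power in each level | Exactly one significant |
|---|---|---|
| 50/50 | 50.8%, 50.8% | 50.0% |
| 70/30 | 65.0%, 33.5% | 54.9% |
| 90/10 | 75.7%, 14.1% | 68.5% |

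For 50/50: 2 × 0.508 × 0.492 = 0.50. Three equal classes, the number Table 7 uses for time, have 36.6% power each, and some but not all are significant in 69.6%.

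**Uniform effect, dichotomized analysis.** The P values in Table 7 belong to this outcome, for which the initial plan needed 3,200 patients. Assume 3,200 also meant 80% power and that both totals treat losses alike. Then the standardized effect at 2,550 is 2.802 × √(2,550/3,200) = 2.50, and overall power is Φ(2.50 − 1.96) = 71%.

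- 50/50: Φ(2.50 × 0.707 − 1.96) = 42% in each half; exactly one significant 2 × 0.424 × 0.576 = 49%.
- 70/30: 55% and 28%; exactly one significant 0.553 × 0.722 + 0.278 × 0.447 = 52%.

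**With an interaction test.** A uniform effect is wrongly called subgroup-specific in 5% per factor. Over four independent factors the chance of at least one such call is 1 − 0.95⁴ = 18.5%. In a simulation of 100,000 trials with four crossed binary factors at 80% overall power, at least one factor had exactly one significant level in 80% (all splits 50/50) to 87% (85/15, 70/30, 60/40, 50/50).

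**Definitions side by side.**

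| Factor | Subgroup text | Table 7 | Elsewhere |
|---|---|---|---|
| Severity (NIHSS) | 1–9, 10–30 | 1–9, 10–30 | Strata: 1–9, above 9 |
| Stroke type | infarction, hemorrhage | ischemic, hemorrhagic, TIA, other | Baseline section: "diagnosis at discharge (infarct, haemorrhage, TIA, or other" |
| Time to treatment | 0–12 h, 12–24 h | 0–6, 6–12, 12–24 h | – |
| Age | named, no cut-points | no row | – |

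**The case against.** Several points on the other side stand.

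- The plan nowhere says that significance will be compared between levels or that a subgroup-specific claim will be made. A reader might infer that the trial is bound to report benefit in one stroke type and not the other; the article does not support that as a forecast. For the ordinal analysis it mentions an odds ratio per level and no P value. The percentages above are the rate of discordant P values, which become wrong conclusions only if someone reads them that way.
- A reader might infer from the ceiling of 30 that the most severe patients are lost. The article does not state the top of the scale, does not say that anyone scored above 30 and gives no count. Any such patient would lack a row in the severity subgroup only and would stay in the intention-to-treat analysis.
- Table 7 might be read as moving the subgroups to the less powerful outcome. It does not: the text plans the ordinal odds ratio in every subgroup and assigns Table 7 to the dichotomized analysis.
- TIA and other are discharge diagnoses, but infarction and hemorrhage are listed under the same heading, so that objection cannot single out the extra rows. The supportable point is that the text has two levels and the table four.
- Treating age as continuous, or dropping P values within levels, would be a preference.

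None of this supplies a test of differing effects. Nor is it detail that a condensed article can leave elsewhere: the article states its subgroup method, and that method does not address the question.

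**Conclusion.** The point holds in this form. The stated method cannot show whether the effect differs between subgroups. Under a uniform effect it gives one significant and one non-significant level in about 50% to 55% of trials for the ordinal outcome at 80% power, and about 49% to 52% for the dichotomized outcome, against 5% per factor for an interaction test. These figures rest on assumed splits from 50/50 to 70/30 and, for the dichotomized outcome, on 3,200 having meant 80% power. More uneven splits raise the ordinal figure (68.5% at 90/10).

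The conflicts in severity, stroke type, time and age are plain on the page. The severity mismatch is minor, and its effect cannot be sized from the article. This is a change that should be made; it does not touch the primary analysis.

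**What to change.** 1. For each prespecified factor, add a treatment-by-factor interaction to the adjusted proportional odds model. Report the interaction P with the level-specific common odds ratios and 95% CIs.
2. State that any claim of a subgroup difference rests on the interaction, not on P values within levels.
3. Define the upper severity class as NIHSS above 9, as randomized.
4. Reconcile stroke type and time between the text and Table 7, and say where TIA and other diagnoses belong. State how age enters the analysis and give it a row.
5. Do this before the code is broken, which the article says will not happen until acceptance.

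The cost is a few model terms, some wording and a revised table. The interaction tests will have low power. With a 50/50 split the difference between levels has twice the standard error of the overall effect, so a difference as large as the overall design effect is detected with power of only Φ(2.802/2 − 1.960) = Φ(−0.559) = 29%. A non-significant interaction should therefore not be read as proof of a uniform effect.
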